### Secondary outcomes

#### Nicotine dependence

Fagerström Test for Nicotine Dependence (FTND) [29] is the most commonly used tool for the assessment of nicotine dependency. The scores obtained on the test permit the classification of nicotine dependence into five levels: very low (0 to 2 points); low (3 to 4 points); moderate (five points); high (6 to 7 points); and very high (8 to 10 points). The instrument evaluates for example time from awakening to the day’s first cigarette, smoking when bed-ridden with illness, and difficulty in refraining from smoking when prohibited.

### MAP-HSS + smoking related complaints of smokers

The MAP-HSS is a ten-item health scale, which was adapted from the Opiate Treatment Index [30]. Each item is scored on a five-point Likert-type scale, ranging from 0 (complaint never present in the previous 30 days) to 4 (complaint always present in the previous 30 days), resulting in a total scale-score ranging from 0 to 40. In addition to MAP-HSS the patients will be asked to scale 16 typical smoking related complaints (for example cold hands and feet, cough, pale skin, pain in the lung). An overall score of physical complaints will be calculated by adding MAP-HSS and the additional smoking related complaints.

### Depression, anxiety and stress (DASS-21)

The DASS21 [31, 32] is a consistent, valid and reliable set of three self-report scales designed to measure the negative emotional states of depression, anxiety and stress. Each of the three DASS scales contains seven items. Patients will be asked to use 4-point severity/frequency scales to rate the extent to which they have experienced each state over the past week. Scores for Depression, Anxiety and Stress will be calculated by summing the scores for the relevant items.

### Quality of life (Euroqol 5D)

The EuroQol-5D [33] is a generic quality-of-life (QoL) instrument which consists of five domains: mobility, self-care, usual activities, pain/discomfort and anxiety/depression. There are three response alternatives for each domain. The EQ-5D index is obtained by means of applying predetermined weights to the five domains. The EQ-5D index is a societal-based numerical quantification of the patients’ health status which can range from 0 (death) to 1 (perfect health status). In addition to the five domains, EuroQol-5D also offers an overall rating for quality of life by means of a visual analogue scale (VAS). The VAS is a vertical line from worst (0) to best state of health (100).

### Smoking status

Smoking status comprises self-reported smoking related variables such as quit attempts (>24 h), number of relapses, or the amount of daily tobacco consumption (cigarettes, self-rolled cigarettes, cigarillos, e-cigarettes). All smoking status variables are based on a standardized questionnaire for Dutch tobacco research [34].

### Adherence

In order to find out how the web-based application is used, real-time logdata will be collected to track individual use. These log files will be used for identifying user profiles and to gain insight into adherence to the application, usage patterns that emerge, and what elements of the application are used. This information will provide insight in how the application (both content and system) matches with its users. In addition, information about the type and number of BCTs taken from the patient’s record, which is kept by the counsellor, will be analysed to calculate the level of adherence.

### Costs

All direct treatment-related costs generated by the care providers and the patients: Costs will be calculated based on hours spent by the counsellors (including for no shows), patients’ travel costs, and maintenance of the web-based infrastructure.

### Baseline predictors and moderators of treatment effect

#### Internet skills

Internet skills will be measured using an online questionnaire based on conceptual definitions for internet skills [17]. This conceptual definition includes two major skill areas (medium-related Internet skills and content-related Internet skills), which contain in total five minor skill areas. Medium-related Internet skills include operational (for example operating an Internet browser or a search engine) and formal (for example maintaining a sense of location when on the Internet) skills. Content-related Internet skills include informational (for example defining search options or queries), communication (for example searching, selecting, reaching and evaluating contacts online) and strategic (for example taking advantage of the Internet) skills. A ten item questionnaire [35] will be used to measure internet skills with a 5-point Likert scale, resulting in a score range from 10 (unskilled) to 50 (highly skilled).

### Readiness to change

Readiness to change will be measured using the algorithm to detect the stage of change in smokers [36]. The expected stop moment (within 1 month versus within 2 or 3 months) offers the possibility to distinguish between the contemplation and preparation stage of change.

### Attitude, social influence and self-efficacy

According to the ASE Model [37, 38] the intention to stop smoking is determined by three motivational factors: Attitude, Social Influence and Self-Efficacy. Attitude [39, 40] refers to the overall evaluation of smoking cessation. Attitude will be measured with an indirect, belief-based scale for perceived pros (four items: improved health for the patient, improved health for the patient’s personal environment, lower risk of lung cancer, improved self-satisfaction) and cons (four items: suffering withdrawal symptoms, missing smoking, less ability to relax, feeling bored). Social influence refers to three distinctive constructs: social norms, perceived behaviour of others and direct support. It will be measured recording if the patient is stimulated to stop smoking by acquaintances, if his/her partners is a smoker and how many of his/her acquaintances are smokers. Self-Efficacy [41] refers to the confidence in the ability to refrain from smoking in specific high-risk situations, i.e. the situations in which the quitter is tempted to relapse. It will be measured recording six typical relapse situations (e.g. stress or party). The three constructs of the ASE model will be measured using standardized questions developed by the former Dutch foundation STIVORO [34, 42].

### Alcohol and substance (mis)use

Alcohol (mis)use will be measured using the Five-shot questionnaire on heavy drinking [43]. Only if a patient declares that he/she is consuming alcohol/substances at all, additional questions will be asked to keep the burden for the patient as low as possible. The additional questions will record the frequency and amount of alcohol consumption, feelings of anger and guilt related to drinking, and if the patient drinks in the morning to cope with hangover. Substance (mis)use will be measured asking for (recreational-)drug use in general. If the patient declares to use (recreational-)drugs additional questions will ask for type of (recreational-)drug and frequency and duration of use.

### Descriptive variables

#### Patient characteristics and medical history

Demographical data (sex, age, nationality, cultural background, marital status, children, housing, education, source of income, main activity) will be collected using an online questionnaire. Medical history will be recorded from medical charts.

### Smoking history

Smoking history will be measured using an online questionnaire from the longitudinal Vlagtwedde-Vlaardingen Study (1965 to 1990) [44] recording the age of first smoking attempts and the numbers of years and number of cigarettes/day that the patient was smoking in each decade.

### Stop smoking history

Earlier attempts to stop smoking will be recorded using an online questionnaire asking: if there were earlier stop smoking attempts; when the last stop smoking attempt was; how long the non-smoking phase was; and when the last stop smoking attempt was, which was successful for more than 24 h.

### Other information of interest

#### Evaluation of treatment

Three month after start of the treatment, at the end of the treatment (6 month after start) and during the follow-up measurements (9 and 15 month after start) patients will be asked to report their experiences with the different aspects of the treatment program. Patients can rate satisfaction with the program by grading all separate types of contact, assessing the overall contact with their counsellors, and reporting their own perception of improvements. In addition, they will be asked to report on adherence, results and benefits, gained insights, the use of co- interventions, and the use of NRT. Furthermore, they will be asked for improvement suggestions.

#### Exhaled carbon monoxide (CO) level

The measurement of exhaled carbon monoxide (CO) level provides an immediate, non-invasive method of assessing smoking status [45]. A breath CO level of 5 ppm is taken as the cut-off between smokers and non-smokers (5 ppm or higher = smoker, less than 5 ppm = non-smoker). Breath CO monitoring will be performed using a piCo Smokerlyzer (Bedfont Instruments: Kent, UK), a portable CO monitor.

The level of exhaled carbon monoxide (CO) level will be recorded because the CO measurement is already part of the treatment so that these data is easily available. Because the validation of the smoking cessation is done with cotinine tests (see above) the CO data will only be used if cotinine measurements are missing and to provide data for future research such as for example comparing different measurement techniques.

### Sample size

For this RCT 344 patients will be needed. This is based on the following assumptions and calculations.

Since we expect that BSCT will be at least non-inferior to TAU concerning prolonged abstinence, we conduct a non-inferiority trial. Furthermore, we expect BSCT to be better at secondary factors such as costs, adherence and satisfaction [46].

Based on previous studies involving smoking cessation treatment within the organization involved in this RCT [4, 5] and meta analyses [3], a cotinine-validated prolonged 12 months’ abstinence rate of 10% (based on intention-to-treat analysis) with TAU is expected. Based on the expected benefits of BSCT the estimated abstinence rate for BSCT is 15%. If BSCT leads to an abstinence rate of not lower than 5% it will be regarded as non-inferior. With a power of 80% and α of 0,025 172 patients per group are needed for this RCT (calculated with PASS).

The 5% criterion is based on the three assumptions described below:A validated prolonged abstinence rate of 5% may still be considered as superior to (1) a non-intervention condition which is estimated at a 1.4% abstinence rate and to (2) a 2.6% abstinence in a minimal intervention condition in clinical populations such as COPD patients [47].In a worst-case scenario, BSCT patients will fail to use the web-based part of the intervention completely, and adhere to the face-to-face component only. This would reduce their exposure to the intervention by 50% compared to full adherence to TAU. Assuming a linear dose–response relationship of intervention intensity and likelihood of abstinence the 10% abstinence rate estimated for TAU would then be reduced by 50% to a 5% abstinence rate.Although a 5% abstinence rate is considerably lower than the estimated 10% in TAU, the secondary benefits of BSCT - such as client satisfaction - need to be taken into account. Thus, even at a lower effectiveness we expect that BSCT can still be the preferred treatment.

Based on the experience that approximately 360 patients per year start a cessation treatment at SRP, it is expected that recruitment, treatment and follow-measurements of the 344 patients needed for this RCT will take 3 to 4 years.

#### Handling of study dropouts

If a subject is prematurely withdrawn or withdraws from participation in the study for whatever reason, the statistical analysis will be conducted following the intention-to-treat principle [48], assuming that missing cases are at their baseline level. This will produce conservative estimates of smoking abstinence but will still allow for treatment outcomes that are based on the entire sample. Patients who fail to keep an appointment will be contacted and if possible, will be rescheduled for another appointment, ideally within 7 days of the missed appointment.

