### Measurements

The time-points of the follow-up measurements are tied to the estimated stop-date, which is appropriate for aid-to-cessation trials [26]. The expected stop-date is 3 months after treatment start, which is later than in common cessation treatments where quitting usually is expected within 1 to 3 weeks. In total there will be four follow-up measurements with measurement 3 and 4 (9 and 15 months follow-up) to be conducted at standard time points (i.e. 6 and 12 months after the expected stop-date):3 months after treatment start, expected stop-date, (3 months follow-up);6 months after treatment start, end of treatment and 3 months after expected stop-date, (6 months follow-up);9 months after treatment start, 3 months after end of treatment, 6 months after expected stop-date, (9 months follow-up); and15 months after treatment start, 9 months after end of treatment, 12 months after expected stop-date, (15 months follow-up).

A measurement schedule can be found in Table 2. The biochemical measurements will be done when the patient is at the hospital for a face-to-face session in week 1 (Exhaled CO; baseline/month 0), week 14 (Exhaled CO & Cotinine level; month 3) and week 22 (Exhaled CO; month 5). For the final biochemical measurement (Exhaled CO & Cotinine Level; month 15) which will take place 12 month after the expected stop date in month 3, the patient will have to return to the hospital. All other assessments will be done using online questionnaires which the patients will complete at home.

**Table 2 Tab2:** Measurement schedule

Variables	Measurement at month					
	0	3	5	6	9	15
Primary outcome						
Cotinine level		X				X
Secondary outcomes						
Nicotine dependence (Fagerström)	X			X	X	
MAP-HSS + smoking related complaints of smokers	X			X	X	X
Depression, anxiety and stress (DASS21)	X			X	X	X
Quality of Life (Euroqol 5D)	X			X		
Smoking status	X	X		X	X	X
Adherence						X
Costs						X
Baseline predictors and moderators of treatment effect						
Internet Skills	X					
Readiness to change	X					
Attitude	X			X	X	
Social Influence	X					
Self-Efficacy	X			X		
Alcohol/substance (mis)use	X			X		
Descriptive variables						
Patient characteristics and medical history	X					
Smoking history	X					
Stop Smoking History	X					
Other information of interest						
Evaluation of treatment		X		X	X	X
Exhaled carbon monoxide (CO) level	X	X	X			X

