## Instruments

### Primary outcome (Cotinine level)

The primary outcome parameter will be biochemically validated prolonged abstinence [26] at 15 months from the start of the smoking cessation treatment. Saliva cotinine level will be measured as biochemical verification of abstinence only by those patients that report quitting smoking in the previous online questionnaires [27]. Prolonged abstinence is defined as having salivary cotinine levels < 20 ng/ml [28] that validate both the self- reported abstinence after the self-chosen stop date – usually 3 months after start - and the self-reported abstinence at 15 month follow-up. Patients not reporting abstinence or with a higher cotinine level on any of these follow-ups will be regarded as smokers as well as patients who are lost to follow-up. A 0,5–1 ml salivary sample will be collected for cotinine assessment by means of a Salivette (Sarstedt AG & Co., Nümbrecht, Germany). Under supervision, patients will have to chew on a cotton swab for 1min to stimulate the saliva flow rate. All saliva specimens will be frozen until assayed and transported to the laboratory for the determination of the cotinine level using a gas chromatography technique.

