### Data analysis/Statistical methods

Baseline characteristics will be displayed as means with standard deviations (SD) or medians with interquartile range (IQR) for continuous variables depending on the distribution of the variable; categorical variables will be displayed as counts with corresponding percentages. Differences between the two treatment groups in terms of continuous variables will be tested by the independent *T*-test or the Wilcoxon rank sum test, depending on the distribution of the variable. Differences in categorical variables will be tested by the Chi-square test or the Fisher exact test.

The non-inferiority between BSCT and TAU in salivary cotinine validated 12 months’ prolonged abstinence rate will be analyzed by calculating the 95% confidence interval of the observed difference in the abstinence rate and by comparing that to the previously defined non-inferiority margin of 5%.

To assess whether BSCT leads to a decrease in treatment costs compared to TAU, an incremental cost-effectiveness ratio (ICER) will be calculated using treatment costs and abstinence rate.

To assess whether BSCT leads to improved satisfaction among patients and counsellors compared to TAU, satisfaction (based on the middle and long-term evaluation) will be tested between the two groups by applying the independent *T*-test or the Wilcoxon rank sum test.

Both baseline predictors - moderators of intervention effect - and dynamic predictors - mechanisms through which effects occur - will be tested using moderator and mediator analyses [49, 50], including all potential co-variates such as nicotine dependence, cognitive determinants (for example attitude and self-efficacy), medical conditions and mental states (for example depression and anxiety), adherence and internet skills.

Whether the level of adherence to BSCT is related to prolonged abstinence will be tested by the independent *T*-test or the Wilcoxon rank sum test.

All analyses will be performed based on the intention-to-treat principle and will be performed in SPSS version 20.0.

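### The baseline-level rule for withdrawn patients is not limited to abstinence; on the repeated scales and in the mediator analyses it imputes zero change and biases the results

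*Protocol article*

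**What the plan says.** The section on handling of study dropouts is triggered by any withdrawal: "If a subject is prematurely withdrawn or withdraws from participation in the study for whatever reason". It then calls for an intention-to-treat analysis, "assuming that missing cases are at their baseline level". No outcome is named or excluded. The reason given is: "This will produce conservative estimates of smoking abstinence but will still allow for treatment outcomes that are based on the entire sample".

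The statistical methods section widens the scope: "All analyses will be performed based on the intention-to-treat principle and will be performed in SPSS version 20.0".

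For the primary outcome, the section on cotinine level has its own rule. Patients who do not report abstinence, or whose cotinine is too high, "will be regarded as smokers as well as patients who are lost to follow-up".

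Table 2 (Measurements) shows which variables have a month-0 value and a later one:

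- MAP-HSS plus complaints, and DASS-21: months 0, 6, 9, 15
- FTND and attitude: months 0, 6, 9
- EQ-5D and self-efficacy: months 0, 6
- Smoking status, including daily consumption: months 0, 3, 6, 9, 15

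The statistical methods section also plans mediator analyses of dynamic predictors. Its list of covariates includes nicotine dependence, attitude, self-efficacy, depression and anxiety. The article names no other missing-data method and no sensitivity analysis.

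**The concern.** For abstinence, the baseline state is smoking, so the rule coincides with counting lost patients as smokers and adds almost nothing. Its practical effect is therefore on the other outcomes with a baseline value, and the stated justification does not reach those. On a scale, the baseline value is not a worst case. It is a single imputed value that fixes the change at zero with no uncertainty. A patient measured at month 6 and lost before month 9 gets the month-0 score at month 9, although a more recent score exists.

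Two things are at stake. Arm comparisons on the scales would mix the treatment effect with the loss pattern. The search for mechanisms of successful quitting, which is a stated objective, would mix a mediator's association with abstinence with the plain fact of having dropped out.

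**Working it through.** **Inputs.** From the article: 172 patients per group, 344 in total; expected abstinence 10% (TAU) and 15% (BSCT). Assumed, because the article gives none: loss rates, mean improvement on a scale, a baseline–follow-up correlation of 0.6, and loss at random. Improvements are in units of the SD of the score, so the variance of change is 2 × (1 − 0.6) = 0.8.

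**The plan's own figure.** The article gives no figure for the scales. Its sample size reproduces: (1.960 + 0.842)² × (0.10 × 0.90 + 0.15 × 0.85) / (0.15 − 0.10 + 0.05)² = 7.85 × 0.2175 / 0.01 ≈ 171 per group, against 172 stated (power at 172: 80.3%). The present point does not touch it.

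**Step 1: expected change under the rule.** With loss *d* and mean change *m*, the arm mean becomes (1 − *d*) × *m*. The estimated difference is (1 − d_B) × m_B − (1 − d_T) × m_T (B = BSCT, T = TAU).

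**Step 2: equal loss.** The true difference is multiplied by (1 − *d*). A true 0.20 SD becomes 0.16 at 20% loss and 0.14 at 30%.

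**Step 3: unequal loss, true difference 0.20 SD (BSCT 0.7, TAU 0.5).**

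- TAU 20%, BSCT 40%: 0.60 × 0.7 − 0.80 × 0.5 = 0.02 (shrunk)
- TAU 40%, BSCT 20%: 0.80 × 0.7 − 0.60 × 0.5 = 0.26 (inflated)
- TAU 30%, BSCT 10%: 0.90 × 0.7 − 0.70 × 0.5 = 0.28 (inflated)

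**Step 4: unequal loss, no true difference.** The false difference is (difference in loss) × *m*. The variance of the imputed change in one arm is (1 − *d*)(0.8 + *m*²) − [(1 − *d*)*m*]². For *m* = 0.8 and loss of 30% versus 50%, the variances are 0.694 and 0.560. The standard error is √(1.254/172) = 0.085, z = 0.16/0.085 = 1.87, and the two-sided 5% test rejects in about 47% of trials.

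| Improvement | Loss | False difference | Rejection rate (normal approximation) | Simulation, 4000 runs |
|---|---|---|---|---|
| 0.5 SD | 30% vs 40% | 0.05 SD | 9% | about 10% |
| 0.5 SD | 30% vs 50% | 0.10 SD | 24% | about 25% |
| 0.8 SD | 30% vs 40% | 0.08 SD | 15% | 14% |
| 0.8 SD | 30% vs 50% | 0.16 SD | 47% | 47% |

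Analysing observed values gives about 5% throughout under the assumed random loss. With *m* = 0 there is no false difference.

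**Step 5: mediator analysis, equal loss.** Take 344 patients, 12.5% counted as abstinent (midpoint of 10% and 15%), and mediator change unrelated to quitting. Let *d* be the share lost before the mediator is measured. Every abstainer is observed, with mean change *m*. Among the 87.5% counted as smokers, a share *d*/0.875 has zero change by rule. The false gap between abstainers and smokers is *m* × *d*/0.875; for *m* = 0.5 and *d* = 0.30 it is 0.17 SD. Simulated false-positive rates for a two-group comparison of mediator change:

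| Improvement | 20% loss | 30% loss | 40% loss |
|---|---|---|---|
| 0.5 SD | 16% | 30% | 49% |
| 0.8 SD | 26% | 54% | 79% |

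Observed cases again give about 5%.

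**The case against.** Several objections have force.

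- **The benefits that matter most are out of reach of the rule.** A reader might infer that it distorts the secondary benefits meant to offset a lower quit rate. The Sample size section and the Discussion name costs, adherence, satisfaction and user friendliness. Table 2 gives none of these a month-0 value, so there is nothing to carry forward. That inference is not supported, and neither is the reading that every analysis is affected.
- **No arm test of the scales is clearly planned.** The general t-test sentence in the statistical methods stands in the paragraph on baseline characteristics, and an unseen analysis plan may say more. This weakens the arm-comparison part. It does not weaken the mediator part, because those analyses are stated.
- **Direction.** A reader might infer that the rule always shrinks a true effect, or that any imbalance in loss produces a false one. Step 3 shows inflation as well, and Step 4 needs a non-zero mean change.
- **Dropouts may really return to baseline.** If so, the rule would be close to right and the observed-case analysis would be the biased one. The 5% figures rest on random loss. This is a reason to keep the rule as a sensitivity analysis, not as the only method.
- **Unequal loss is not shown.** The Background does call poor engagement common in web-based treatment, but argues that blending offsets it. Questionnaires are online in both arms, with reminders and a paper option. The loss gaps used here are illustrations.
- **Smaller points.** The rule fills missing values and removes no observed score. The EQ-5D scale sets death at 0, but the article does not discuss deaths, EQ-5D has one follow-up, and the planned cost-effectiveness ratio uses abstinence. Nothing of weight rests on that.

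**Conclusion.** The point holds for the scales and mediators that have a baseline value. The article states the rule affirmatively, places no limit on it and defends it only for abstinence. This is a poorly chosen stated method, not detail left to an analysis plan. Where scores change on average, arm comparisons are biased by a factor of 1 minus the loss rate under equal loss, and in either direction under unequal loss. The mediator analyses acquire a false association with abstinence even under equal loss, because one patient is imputed twice: as unchanged and as a smoker.

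The sizes shown depend on assumed loss, improvement, correlation and random loss, and they illustrate the mechanism; they do not predict this trial's results. The primary outcome is not affected beyond its own rule for lost patients, and the sample size stands. The change is worth making for the secondary objectives, but it does not threaten the main conclusion.

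**What to change.** In the section on handling of study dropouts, limit the baseline-level rule to smoking abstinence. For the other variables with a baseline value:

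- **Scales and mediators with several follow-ups:** a likelihood-based repeated-measures model using all observed months (arm, month, arm by month, baseline value), or multiple imputation that uses the earlier follow-ups.
- **One follow-up only (EQ-5D, self-efficacy):** baseline-adjusted ANCOVA with multiple imputation.
- **Mediator analyses:** the same treatment of missing mediator values, so that a dropout is not assigned zero change as well as smoking.
- **Sensitivity analysis:** keep baseline carried forward, and report loss by arm and month beside it.

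The cost is analysis wording and standard models; no new data are needed. The downside is a missing-at-random assumption for the scales, which the retained sensitivity analysis probes.

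### Counting missing patients as smokers under an intention-to-treat-only analysis is conservative for each arm's quit rate, but not necessarily for a non-inferiority comparison against a fixed 5-point margin

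*Protocol article*

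**What the plan says.** Four statements in the protocol article together fix the primary analysis.

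- **Primary outcome (Cotinine level):** patients who do not report abstinence, or whose cotinine is too high, "will be regarded as smokers as well as patients who are lost to follow-up".
- **Handling of study dropouts:** missing cases are set to their baseline level, which for this outcome means smoking. The justification reads "This will produce conservative estimates of smoking abstinence but will still allow for treatment outcomes that are based on the entire sample".
- **Data analysis/Statistical methods:** the 95% confidence interval of the difference in abstinence is set against a margin of 5%. The section ends with "All analyses will be performed based on the intention-to-treat principle". It names no per-protocol set and no second treatment of missing outcomes.
- **Sample size:** a cotinine-validated "abstinence rate of 10% (based on intention-to-treat analysis) with TAU is expected", 15% is assumed for BSCT, and "If BSCT leads to an abstinence rate of not lower than 5% it will be regarded as non-inferior".

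**The concern.** In a superiority trial, counting losses as failures usually makes the claim harder to reach. In a non-inferiority trial the claim is that the arms are close, so anything that pulls the two rates together helps it. Loss that is equal in both arms and unrelated to outcome multiplies both rates, and hence their difference, by the retained fraction, while the margin stays at 5 points. Missed sessions in TAU would act in the same direction under intention to treat.

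Loss is a practical possibility here. Success requires validated abstinence after the stop date and again at month 15. The month-15 sample needs a separate hospital visit nine months after treatment ends. The exhaled-CO backup is taken at that same visit, so it does not recover a patient who stays away.

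At stake is the primary conclusion. The Discussion says that non-inferiority together with secondary benefits should warrant dissemination to practice.

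**Working it through.** **Inputs from the protocol article.** TAU 10% (stated as intention-to-treat based), BSCT 15%, margin 5 points, α 0.025, power 80%, 172 per group, 1:1 allocation, decision by the 95% confidence interval. The loss rate is not given, so 0% to 40% is assumed. The interval method is not named, so Wald and Farrington-Manning score results are both shown.

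**1. The plan's own figure.** n = (1.96 + 0.842)² × [0.10×0.90 + 0.15×0.85] / (0.05 + 0.05)² = 7.85 × 0.2175 / 0.01 ≈ 171 per group, against 172 stated. It reproduces. Power at 172 is 80.3% by the normal approximation.

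**2. Effect of the rule on the difference.** With true rates pB and pT, loss mB and mT, and loss unrelated to outcome:

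observed difference = pB(1 − mB) − pT(1 − mT).

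With equal loss m this is (pB − pT)(1 − m). A true deficit of 5 points appears as 4.0, 3.5 or 3.0 points at 20%, 30% or 40% loss.

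**3. False non-inferiority rate.** All pairs of binomial counts with n = 172 per arm were enumerated. The probabilities of those pairs whose 95% lower limit lies above −5 points were summed.

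*Observed TAU held at 10%, with a true 5-point deficit.* True TAU = 0.10/(1 − m), true BSCT = true TAU − 0.05, observed BSCT = true BSCT × (1 − m).

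| Loss per arm | True TAU / BSCT | Observed TAU / BSCT | Wald | Score |
|---|---|---|---|---|
| 0% | 10.0 / 5.0 | 10.0 / 5.0 | 3.1% | 2.4% |
| 20% | 12.5 / 7.5 | 10.0 / 6.0 | 6.1% | 5.2% |
| 30% | 14.3 / 9.3 | 10.0 / 6.5 | 8.2% | 7.1% |
| 40% | 16.7 / 11.7 | 10.0 / 7.0 | 10.8% | 9.6% |

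The Wald figure of 3.1% at zero loss, above the nominal 2.5%, comes from the interval method and not from missing data.

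*True rates held at 10% and 5% instead.* At 20%, 30% and 40% equal loss the rates are 7.1%, 10.9% and 16.6% (Wald), or 5.2%, 7.8% and 11.8% (score).

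**4. Dependence on who is missing** (true rates 10% and 5% overall). Let missing patients quit at a fraction f of the observed rate. Both observed rates are then the true rates times (1 − m)/[(1 − m) + mf].

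| f | Wald, 20% loss | Wald, 30% loss |
|---|---|---|
| 0 (all missing smoke) | 3.1% | 3.1% |
| 0.25 | 3.9% | 4.6% |
| 0.5 | 4.9% | 6.5% |
| 1 | 7.1% | 10.9% |

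**5. Dependence on balance** (true rates 10% and 5%, loss unrelated to outcome). The difference stays at −5 points when 0.05·mB = 0.10·mT, that is when BSCT loss is twice TAU loss.

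| BSCT loss / TAU loss | Observed difference | Wald | Score |
|---|---|---|---|
| 20% / 10% | −5.0 | 3.2% | 2.3% |
| 40% / 20% | −5.0 | 3.4% | 2.2% |
| 30% / 20% | −4.5 | 5.0% | 3.5% |
| 20% / 30% | −3.0 | 14.6% | 11.0% |

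Above a ratio of two the rule works against BSCT. In general the ratio is pT/pB, so it is lower when the two true rates are closer.

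**The case against.** **The wording.** A reader might infer that the protocol calls its non-inferiority comparison conservative. It does not. The sentence speaks of estimates of abstinence, and for each arm's rate it is right. What stands is narrower: it is the only justification given for the rule, and it does not address the comparison that decides the trial.

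**The scale of the margin.** The 10% for TAU is stated to be intention-to-treat based, and one rationale for the 5% floor halves that rate. Read that way, rate and margin already include losses counted as smokers, and at 10% against 5% on that scale the error stays at 3.1% (Wald) or 2.4% (score). This stands at the planned rates. It protects the trial only as far as its loss resembles that behind the 10%. Further loss lowers both rates against the same 5 points.

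**The direction.** A reader might also infer that the rule always inflates false non-inferiority. Steps 4 and 5 show that it does not. The Background names poor engagement as a common problem of web-based treatment, so higher loss in BSCT cannot be excluded. The protocol also plans reminders, telephone contact, paper questionnaires and rescheduling to limit loss.

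**Adherence.** Non-use of online sessions occurs only in BSCT and would widen a deficit. The Sample size section builds that case into its margin argument. However, that argument compares it with full adherence to TAU, which missed TAU sessions would undercut.

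**The analysis plan.** It is not shown and may hold sensitivity analyses. Imputation keeps every randomised patient and is compatible with intention to treat. A per-protocol analysis is harder to square with a statement that covers all analyses.

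**Conclusion.** The point holds conditionally. The stated rule is conservative for each arm's abstinence rate and is not shown to be so for the non-inferiority comparison. Where loss is similar in both arms or higher in TAU, and some of the missing have quit, it makes non-inferiority easier to claim, and no analysis stated in the protocol would reveal this.

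The size cannot be fixed from the document. The increase to 6.1%, 8.2% or 10.8% rests on four assumptions: 20%, 30% or 40% loss, equal in both arms and unrelated to outcome; an observed TAU rate of 10%; a margin meant for true quit rates; and a Wald interval. Relaxing them can take the inflation to nothing or reverse it, while higher loss in TAU makes it worse. The documents do not show that the primary analysis is invalid or that attrition will produce its result. They support adding analyses around it, not replacing it.

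**What to change.** 1. Keep intention to treat with missing counted as smoking as the primary analysis.
2. In Data analysis/Statistical methods, add two supportive analyses of the primary outcome:
   - a per-protocol analysis of patients who meet a pre-stated attendance threshold in the allocated mode;
   - multiple imputation of abstinence by arm, with a tipping-point range that lets the quit rate among the missing differ between arms.
3. Report for each whether the lower 95% limit stays above −5 points, and interpret a non-inferiority claim cautiously if they disagree. Requiring success in all of them is a debatable design choice and is not needed to meet this point.
4. In Handling of study dropouts, state that 'conservative' applies to arm-level abstinence rates and not to the non-inferiority comparison.

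**Cost.** Wording changes and a few extra analyses of data the trial already plans to collect, with no additional patients. The conclusion may be less clear-cut. The per-protocol set is selected after randomisation and can be biased in either direction, so it can only be supportive.
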